## Abstract

**Background:**

Although a satisfactory disease control is nowadays achievable in most patients with JIA, a substantial proportion of them still do not respond adequately or reach long-term drug-free remission. According to current recommendations, treatment should be escalated in subsequent steps. A different approach is based on the assumption that the initial start of an aggressive therapy may take advantage of the “window of opportunity” and could alter the biology of the disease, leading to an improvement of long-term outcomes, including the prevention of cumulative joint damage.

**Objectives:**

This randomised clinical trial aims to compare the effectiveness of a conventional therapeutic regimen, based on treatment escalation and driven by the treat-to-target approach, with that of an early aggressive intervention based on the initial start of a combination of conventional and biological DMARDs.

**Methods:**

JIA patients with oligoarthritis or RF negative polyarthritis aged more than 2 years and with less than 4 months of disease course will be included in the study. Children will be randomised into two arms: patients in Step-up arm with less severe oligoarthritis will undergo an intra-articular corticosteroid injection (IACI) in all affected joints; patients with polyarthritis or severe oligoarthritis will receive IACI and methotrexate. Subsequent treatment will follow a standardised protocol based on the patients’ level of disease activity measured with the JADAS, according to a treat-to-target strategy. Patients in Step-down arm will receive a 6-month early combined treatment (methotrexate plus IACI for less severe oligoarthritis, methotrexate plus etanercept for severe oligoarthritis and polyarthritis). The primary endpoint is the frequency of achievement of the status of clinical remission (i.e. persistence of inactive disease for at least 6 months) at the 12-month visit. Safety events, physician-centred measures and parent/patient-reported outcomes will be collected through the Paediatric Rheumatology International Trials Organisation on line database.

**Expected results:**

The STARS trial aims to provide important evidence supporting the first-line treatment choices in the care of children with oligoarticular and polyarticular JIA. If the superiority of an early aggressive therapy will be demonstrated, this will demand further studies on the biological definition of the window of opportunity for JIA.

**Trial registration:**

The Trial is registered on the ClinicalTrials.gov registry (NCT03728478) on the 31st October 2018 and EU Clinical Trials Register on the 14th May 2018 (EudraCT Number: 2018–001931-27).

## Background

### Rationale

The “comparison of STep-up and step-down therapeutic strategies in childhood ARthritiS” (STARS) trial aims to investigate whether an early aggressive therapeutic intervention, based on the initial start of synthetic and biologic DMARDs (Step-down strategy), is superior to an approach based on treatment escalation conducted following the treat-to-target principle [1] (Step-up strategy), in children with juvenile idiopathic arthritis (JIA). The effectiveness of the two strategies will be assessed by comparing their ability to induce sustained clinical disease remission on/off treatment.

With a different approach, both interventions aim to obtain a quick and robust disease control and maintain it over time. Historically and according to the ACR recommendation [2], the treatment of JIA is escalated in subsequent steps. In general, treatment begins with NSAIDs or intra-articular joint injections, which, in case of insufficient effectiveness or disease flare, are replaced by or associated with a synthetic DMARD, such as methotrexate (MTX), sulphasalazine or leflunomide. In case of inadequate response and according to the current label indication, a biologic DMARD is usually prescribed in substitution of or in conjunction with the synthetic DMARD.

The treat-to-target strategy was first advocated for the treatment of adult rheumatoid arthritis in 2010, based on its successful use in chronic conditions such as hypertension and diabetes mellitus. This approach is based on the assumption that frequent adjustment of therapy intended to reach minimal levels of disease activity will lead to an improvement in patient outcomes according to quantitative indices [3, 4]. Key components of the treat-to-target include the explicit definition of a therapeutic target (such as clinical remission or low disease activity) at the beginning of the treatment and the verification of its achievement at each subsequent visit. If the target is reached the treatment is left unchanged, whereas if the target is not reached the treatment is intensified. The 2010 EULAR recommendations [5] for the management of rheumatoid arthritis were centered on the treat-to-target strategy, as were the later joint ACR/EULAR recommendations. A 2013 update of the EULAR recommendations [6] went even further in highlighting the treat-to-target as a fundamental component of treatment strategies. In 2018, the first recommendations for the application of the treat-to-target study to the care of children with JIA were developed. Although recommendations could not be based on high level of evidence, they reached significant agreement in an international task force of pediatric rheumatologists with a large experience in the field [4]. Evidence supporting the treat-to-target strategy is now increasing. The recent Best for Kids study [7], which aimed to compare three different treatment strategies for JIA (synthetic DMARD monotherapy, synthetic DMARD and bridging prednisone, and a combination of synthetic and biologic DMARDs), showed that regardless of initial specific treatments, after 24 months of treatment-to-target aimed at drug-free inactive disease, 71% of recent-onset patients with JIA had inactive disease and 39% were drug free. A non-randomised study showed that patients treated according to a treat-to-target protocol had a higher chance to achieve remission in comparison to a matched cohort [8]. A quality improvement initiative in a tertiary care medical centre showed that intense patient monitoring, target attestation and standardization of clinical decision support lead to better patient outcomes [9].

Early intensive therapy in JIA during the so-called window of opportunity is believed to be able to alter the biology of the disease and improve long-term outcomes, including prevention of cumulative joint damage [4, 10, 11]. In systemic JIA, early anti-IL-1 therapy was found to quickly lead to inactive disease and facilitate sustained disease control. Indeed, in a cohort of steroid-naive patients with new-onset systemic JIA treated with IL-1 receptor antagonist therapy, 85% of patients had achieved inactive disease or an ACR paediatric 90% response by 3 months of treatment. The benefits of early treatment with other agents and in other JIA categories are less clear, but have been increasingly suggested for polyarticular JIA. In the ACUTE-JIA trial [10], initiation of anti-TNF therapy plus MTX in DMARD-naive patients with polyarticular JIA was more effective in achieving minimally active or inactive disease than MTX alone or MTX plus hydroxy-chloroquine and sulfasalazine. The TREAT trial [11] showed a benefit with an early aggressive strategy, even though it failed to reach its primary end-point. More recently, a trajectory analysis of 400 patients in the Start Time Optimization of Biologics in Polyarticular JIA study demonstrated that starting a biologic treatment within 3 months of baseline assessment is associated with a more rapid achievement of inactive disease in subjects with untreated polyarthritis [12].

The approach proposed in the present trial represents a step forward as compared to most previous therapeutic studies in JIA, as it does not involve the exposure of children to a placebo. Furthermore, it does not assess the effectiveness of treatments in terms of mere percentage improvement in disease symptoms or achievement of a particular disease state at a single time point but it evaluates the ability of treatments to induce and maintain the state of clinical remission over time. In addition, the trial includes the administration of systemic corticosteroids only in the most severe disease subsets (i.e., those characterised by involvement of hip or cervical spine joints). Of note, a recent trial of early aggressive therapy in polyarticular JIA [11] has been subjected to major criticism owing to the choice of giving oral prednisone to all children in the more aggressive arms.

The design of the STARS trial is innovative and aims to address the major unmet needs in the current management of JIA in the real world of daily clinical care. For instance, it is still unclear whether progressive treatment intensification based on the magnitude of therapeutic response over time is more advantageous than initial administration of an aggressive therapy in terms of achievement and maintenance of complete disease control. Furthermore, it is still debated whether intra-articular corticosteroid therapy leads to better results with lower side effects than systemic corticosteroid administration. The Step-up approach will be conducted following the treat-to-target strategy, a novel method of management which has proved effective in the care of adult patients with rheumatoid arthritis and has shown better therapeutic results than conventional regimens in several controlled trials [13]. Note that recommendations for the use of the treat-to-target strategy in adults with rheumatoid arthritis have been recently issued by the European League Against Rheumatism (EULAR) [14]. Although there is an increasing interest among pediatric rheumatologists in the adoption of the treat-to-target strategy, this approach has not been hitherto implemented in the management of children with JIA.

In conclusion, the primary aim of the trial is to scrutinise the ability of the two therapeutic interventions to induce complete disease control early and to maintain it over time. Among other objectives, investigating their capacity to reduce the need for the later introduction of biologic agents, which would lead to a reduction in the costs for the national health-care system and in the exposure of children to the potential (and still unclear) long-term side effects of these medications. The achievement of the main endpoints of the trial might also result in the decreased need of repeated intra-articular corticosteroid joint injections (IACI), which might lessen the child’s and parents’ related emotional distress and the financial and organizational burden required by these procedures under sedation or general anaesthesia.

Specific aim of this work is to present the STARS trial to the international pediatric rheumatology community and to foster participation in the trial outside the Italian borders.

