### Interventions

After the screening visit and recording of informed consent, patients will be randomised into two treatment arms: “Step-up” and “Step-down”. Patients in the Step-up arm will be treated according to a conventional strategy based on treatment escalation and driven by the treat-to-target strategy. Patients in the Step-down arm will be treated with an early, combined, aggressive therapy for 6 months.

In the Step-up arm, less severe patients will receive IACI in all affected joints without systemic therapies. If the juvenile arthritis disease activity score-10 (JADAS10) state of minimal disease activity (MiDA) after 3 months or the JADAS10 inactive disease (ID) state at 6 months are not reached, treatment with MTX will be started preferably subcutaneously in a single weekly dose of 15 mg/m2 (max 20 mg) and IACI can be repeated. Then, if the states of JADAS MiDA after 3 months or JADAS ID at 6 months are not reached, treatment with an anti-TNF agent in a single weekly dose of 0.8 mg/kg (max 50 mg) subcutaneously will be started. More severe patients in Step-up arm will receive IACI(s) and MTX as a first step and then escalate therapy with the same pathway, adding an anti-TNF treatment as a second step and switching to a different biologic medication as a third step (Fig. 1).

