**Fig. 1 Fig1:**
[figure not shown]
Step-up arm design. T2T Group 1: Subjects with oligoarthritis without features of poor prognosis. T2T Group 2: Subjects with oligoarthritis with features of poor prognosis and subjects with polyarthritis. JADAS: Juvenile Arthritis Disease Activity Score-10. JADAS< 50%: improvement of JADAS10 of at least 50%, JADAS<ID: JADAS10 score below inactive disease cutoff. JADAS<HDA: JADAS10 score under HDA cutoffs. JADAS>HDA: JADAS10 score above HDA cutoffs. If at the visit 3 months after step 1, 2, and 3 the patient is improved by less than 50% in the JADAS score, but he/she reaches the JADAS state of minimal disease activity, treatment is not escalated ID = inactive disease, HDA = high disease activity. CR on med.: clinical remission on medication. IACI: intra-articular corticosteroids injection. +MTX: start methotrexate (repeating IACI or adding a short course of prednisone can be considered). +TNF: add therapy with an anti-TNF agent (repeating IACI or adding a short course of prednisone can be considered). +TNF2: replace anti-TNF agent with another an anti-TNF agent or with an anti IL-6 agent (repeating IACI or adding a short course of prednisone can be considered)

Patients allocated to the Step-down arm (Fig. 2) will receive an early combined treatment (MTX plus IACI for less severe oligoarthritis, MTX plus etanercept for severe oligoarthritis and polyarthritis). After 6 months, if JADAS10 ID is achieved, less severe patients will have MTX discontinued, whereas more severe patients will stop etanercept and continue MTX. Children in Step-down arm experiencing a worsening from the baseline of the JADAS10 at 3 months, not achieving JADAS10 ID at month 6, or losing the state of ID after month 6 will be considered as treatment failures and will change treatment according to the attending physician decision.

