**Fig. 2 Fig2:**

Step-down arm design. Step A is start methotrexate plus intra-articular joint injections for oligoarthritis without features of poor prognosis, methotrexate plus etanercept and optional intra-articular joint injections for other patients. Step B is withdraw methotrexate for oligoarthritis without features of poor prognosis, withdraw etanercept and continue methotrexate for other patients. JADAS: Juvenile Arthritis Disease Activity Score-10. JADAS<ID: JADAS10 score below inactive disease cutoff. CR on med.: clinical remission on medication

For the IACIs, triamcinolone hexacetonide will be administered at a dose of 1 mg/kg (max 40 mg) in the hips, knees and shoulders, at the dose of 0.75 mg/kg (max 30 mg) in the ankles and elbows, at the dose of 0.5 mg/kg (max 20 mg) in the wrists; methylprednisolone acetate will be administered at the dose of 1 mg/kg (max 40 mg) in the subtalar and inter-tarsal joints and at the dose of 5–10 mg, depending on the size of the child, in the small joints of hands and feet. A course of oral prednisone instead of or in addition to joint injection can be prescribed in case hip, temporomandibular joints or cervical spine are involved, or in case more than four joints are affected or joint injections cannot be performed.

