The cumulative time on therapy will be calculated as the time difference (in days) between the date of the visit on which the patient will start a systemic medication (synthetic or biologic DMARDs or steroids) and the date on which he/she will be observed to no longer be in treatment with a systemic medication or completed the study. We assume that if a patient does not receive medications at 2 consecutive visits, the patient had not received medications everyday between these visits. Patients initiating a systemic treatment at the final visit of the study will contribute a single day of time in therapy. The mean percentage of time spent on therapy per patient will be recorded and compared between the 2 arms.	
Rate of flares	
The rate of patients who develop flare, defined as the recurrence of active disease after attaining inactive disease at last visit according to JADAS or JIA ACR definition, and the number of flares and the time to flare per patient will be recorded and compared. Notably, all patients prescribed intra-articular injections, synthetic or biologic DMARDs or systemic steroids will be considered as flare independently from JADAS or ACR criteria.	
Rate of uveitis onset	
The rate of patients who develop uveitis according to the Standardized Uveitis Nomenclature (SUN) will be recorded and compared between the 2 arms. The rate of patients requiring systemic medications for treatment of uveitis will be also recorded and compared between the 2 arms. However, these patients will be excluded from the study and followed for safety only.	

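### The Rationale states a narrower limit on systemic steroids than the Interventions section applies, and the time-on-therapy wording over-counts a short prednisone course given at entry

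*Protocol article*

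**What the plan says.** Four places in the protocol article bear on this.

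- **Background, Rationale.** As a feature that sets this trial apart from earlier ones, "the trial includes the administration of systemic corticosteroids only in the most severe disease subsets". The sentence then defines those subsets as children with hip or cervical spine involvement.
- **Methods, Interventions, default regimens.** In Step-up, "less severe patients will receive IACI in all affected joints without systemic therapies". By contrast, "More severe patients in Step-up arm will receive IACI(s) and MTX as a first step". Step-down children start on combined treatment: "MTX plus IACI for less severe oligoarthritis, MTX plus etanercept for severe oligoarthritis and polyarthritis".
- **Methods, Interventions, after the Fig. 2 legend.** "A course of oral prednisone instead of or in addition to joint injection can be prescribed" and the conditions are "in case hip, temporomandibular joints or cervical spine are involved, or in case more than four joints are affected or joint injections cannot be performed". No limit by arm, severity group or visit is given.
- **Endpoints, Table 3, Time spent on therapy.** The clock starts on "the date of the visit on which the patient will start a systemic medication (synthetic or biologic DMARDs or steroids"). It stops on "the date on which he/she will be observed to no longer be in treatment with a systemic medication", or at study completion. The mean percentage of time on therapy is compared between the arms.

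Table 1 (Study population) decides who is less severe. Oligoarthritis becomes more severe with hip or cervical spine arthritis, or with ankle or wrist arthritis plus a raised ESR. Neither temporomandibular arthritis nor infeasible injection is on that list.

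**The concern.** The Rationale presents restricted steroid use as an advance, and its next sentence contrasts it with a trial criticised for giving oral prednisone to all children in its more aggressive arms. If the working rule is wider than the claim, readers are told something about the design that is not so. These readers include centres outside Italy that the article hopes to recruit.

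There is also a measurement question. Less severe Step-up is the only entry regimen without a systemic drug, so it is the only one in which an entry course of prednisone adds to time on therapy. If the endpoint wording lengthens a short course, the excess falls on one arm of a between-arm comparison.

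**Working it through.** The article gives no figure for this point, so there is none to reproduce. The check is a comparison of texts, followed by arithmetic on assumed inputs.

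**Step 1: is the stated restriction true of the working rule?**

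| Condition for oral prednisone | In Rationale | In Interventions | Possible in a less severe child at entry (Table 1) |
|---|---|---|---|
| Hip or cervical spine | yes | yes | no, makes the child more severe |
| Temporomandibular joint | no | yes | yes |
| More than four joints | no | yes | no, if polyarthritis means five or more joints (assumed) |
| Injections cannot be performed | no | yes | yes |

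Three conditions go beyond the Rationale, and two of them can apply to a less severe child at entry. On the assumed meaning of polyarthritis, which the article does not define, every child with polyarthritis in both arms is eligible for prednisone under the third row.

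**Step 2: who can gain time on therapy from an entry course?**

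More severe Step-up and both Step-down groups start methotrexate at entry. A concurrent prednisone course therefore adds no time for them. Only less severe Step-up starts at zero. This holds for entry courses only: a less severe Step-down child who is off methotrexate after month 6 and then gets prednisone alone could be over-counted in the same way.

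**Step 3: credited against actual time, per child**

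Assumptions: a course of 14 to 28 days, and no visit before month 3 (the first treatment decision in Interventions; the article gives no full visit schedule).

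- Credited to the month-3 visit: 91/365 = 24.9%.
- Actual: 14/365 = 3.8% to 28/365 = 7.7%.
- Excess: (91 − 28)/365 = 63/365 = 17.3 points, to (91 − 14)/365 = 77/365 = 21.1 points.

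The visit-based reading is natural because the start is tied to a visit, the stop to being observed off treatment, and the next sentence of the same entry infers status between consecutive visits.

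For scale, a less severe child at target without escalation contributes 0% in Step-up and 6/12 = 50% in Step-down (methotrexate for months 0 to 6).

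**Step 4: excess in the mean**

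Group excess = f × (17.3 to 21.1), where f is the share of less severe Step-up children given prednisone at entry (assumed; the article gives no frequency). Arm excess = group excess × 57/113 = group excess × 0.504. This applies the overall less severe share in Trial status to the Step-up arm.

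| f | Group excess (points) | Step-up arm excess (points) |
|---|---|---|
| 5% | 0.86 to 1.05 | 0.44 to 0.53 |
| 10% | 1.73 to 2.11 | 0.87 to 1.06 |
| 20% | 3.45 to 4.22 | 1.74 to 2.13 |

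**The case against.** The best reply is that the Interventions section is coherent. The regimen without systemic therapy is the default, and the prednisone paragraph is a permissive exception. A child who cannot be injected cannot receive the default and needs a fallback. **That stands.** A reader might infer that Interventions contradicts itself, but the text reads well as rule and exception, and only a linking clause is missing. It does not rescue the Rationale, which says only and lists two sites.

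Second, Table 3 names steroids as systemic medication, so a child on prednisone is on therapy and should be counted. **That stands too.** A reader might infer that counting entry prednisone biases the endpoint against Step-up. It does not: the days actually on prednisone are real exposure, and that only Step-up can gain them reflects the regimens. The defect is limited to days credited after the course has ended. Splitting the endpoint into DMARD time and steroid time would therefore be a preference, not a correction. The prednisone option in the Fig. 1 legend accompanies steps at which systemic treatment is being started or continued, so it does not bear on entry courses.

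Third, the size rests on assumed frequencies, course lengths and visit timing, and ending at the visit is not the only possible reading, since medication history is taken at each visit and stop dates may be recorded. This is fair, and it keeps the point small. It also shows that the remedy is cheap.

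**Conclusion.** The point holds in two limited parts.

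1. The Rationale misstates the steroid rule. This needs no assumption: temporomandibular involvement and infeasible injection are permitted reasons for prednisone and fall outside hip or cervical spine disease. The further statement that all children with polyarthritis are eligible rests on the assumed five-joint definition. Eligible does not mean treated, and the article does not say that prednisone is given to all of them.

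2. As worded, time on therapy can credit a 14 to 28 day entry course with about 91 days, an excess of 17.3 to 21.1 percentage points of the year for that child. For entry courses the excess falls only on less severe Step-up children. In the Step-up arm mean it stays below about 2.2 points even at an assumed 20% use, which is small beside the 0% versus 50% contrast for less severe children at target.

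A reader might go on to infer an effect on the primary endpoint. The documents do not support that: the endpoint is clinical remission on or off medication, so how prednisone time is counted does not enter its definition. Severity is at the low end of minor.

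**What to change.** Make three wording changes.

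- **Rationale:** replace the hip-or-cervical-spine limit with the full list of conditions given in Interventions.
- **Interventions, less severe Step-up:** after the statement that no systemic therapy is given, add: except oral prednisone under the conditions below.
- **Table 3, Time spent on therapy:** state that a systemic steroid course ends at its recorded stop date, taken from the medication history, and not at the next visit.

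The cost is a few sentences. No new visits are needed, because medication history is already collected at each trial visit, but stop dates must be recorded there and used. The price to the sponsor is that the claim of restricted steroid use becomes less favourable.
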